## Abstract

**Background:**

Over the past four decades, advances in HIV treatment have contributed to a longer life expectancy for people living with HIV (PLWH). With these gains, the prevention and management of chronic co-morbidities, such as diabetes, are now central medical care goals for this population. In the United States, food insecurity disproportionately impacts PLWH and may play a role in the development of insulin resistance through direct and indirect pathways. The Nutrition to Optimize, Understand, and Restore Insulin Sensitivity in HIV for Oklahoma (NOURISH-OK) will use a novel, multi-level, integrated framework to explore how food insecurity contributes to insulin resistance among PLWH. Specifically, it will explore how food insecurity may operate as an intermediary risk factor for insulin resistance, including potential linkages between upstream determinants of health and downstream consequences of poor diet, other behavioral risk factors, and chronic inflammation.

**Methods/design:**

This paper summarizes the protocol for the first aim of the NOURISH-OK study, which involves purposeful cross-sectional sampling of PLWH (n=500) across four levels of food insecurity to test our conceptual framework. Developed in collaboration with community stakeholders, this initial phase involves the collection of anthropometrics, fasting blood samples, non-blood biomarkers, 24-hour food recall to estimate the Dietary Inflammatory Index (DII^®^) score, and survey data. A 1-month, prospective observational sub-study (total n=100; n=25 for each food security group) involves weekly 24-hour food recalls and stool samples to identify temporal associations between food insecurity, diet, and gut microbiome composition. Using structural equation modeling, we will explore how upstream risk factors, including early life events, current discrimination, and community food access, may influence food insecurity and its potential downstream impacts, including diet, other lifestyle risk behaviors, and chronic inflammation, with insulin resistance as the ultimate outcome variable. Findings from these analyses of observational data will inform the subsequent study aims, which involve qualitative exploration of significant pathways, followed by development and testing of a low-DII^®^ food as medicine intervention to reverse insulin resistance among PLWH (ClinicalTrials.gov Identifier: NCT05208671).

**Discussion:**

The NOURISH-OK study will address important research gaps to inform the development of food as medicine interventions to support healthy aging for PLWH.

## Introduction

The fourth decade of the HIV epidemic marks many milestones in the treatment and management of HIV as a chronic disease. These medical advances have paved the way for new questions about how to optimize the health span for people living with HIV (PLWH), including chronic co-morbidity risk reduction and management. PLWH experience higher rates of diabetes compared to the general US population (1), with one in ten PLWH having diabetes (1) and another three in ten PLWH having prediabetes (2). The underlying insulin resistance that leads to diabetes is also associated with other co-morbidities of concern for PLWH, such as non-alcoholic fatty liver disease (3) and cognitive decline (4). Insulin resistance occurs when a person’s tissues become resistant to insulin-induced glucose uptake (5) and its causes among PLWH are likely multifactorial (5). Non-modifiable risk factors include age and family history, as well as factors specific to HIV, such as certain antiretroviral medications (6, 7) and possibly HIV infection itself (1). Modifiable risk factors for insulin resistance include central adiposity, physical inactivity, and poor diet. Although intervention data are lacking for PLWH, insulin resistance can often be reversed in the general population through healthy eating and other lifestyle behavior changes (6).

### Unpacking the upstream: Contextualizing food insecurity as a risk factor for insulin resistance

While identification of modifiable risk behaviors for insulin resistance among PLWH is an important clinical question, it is unlikely to result in risk reduction unless the context of these behaviors is elucidated and addressed through additional resources and supports. Among PLWH, those with limited financial resources are disproportionately insulin resistant (8). Food insecurity, the uncertain or limited household availability of a healthy food supply, may provide insightful context for understanding predisposition to insulin resistance among low-income PLWH. Food insecurity disproportionately affects PLWH and is a well-established predictor of HIV risk, transmission, and treatment outcomes that operates through nutritional and non-nutritional pathways (9). In the general population, food insecurity is associated with insulin resistance and diabetes, as well as modifiable risk factors for insulin resistance, including inflammatory diets (10), inadequate sleep (11), and physical inactivity (12).

Since food insecurity is a multidimensional, graded phenomenon of increasing severity, each dimension may have distinct influence on health behaviors and outcomes. Therefore, its influence may be understood best when the construct is treated as an ordinal or continuous variable rather than a dichotomous one. For example, marginal and low food security may contribute to insulin resistance *via* overnutrition through the consumption of a pro-inflammatory diet, consisting of low-cost, energy-dense foods with low fiber and micronutrient content (10, 13). In contrast, very low food security can result in undernutrition due to physical hunger and unintentional weight loss. Very low food security may contribute to insulin resistance through other changes in body composition, such as loss of lean muscle mass and possibly functional and morphologic changes in the intestine including intestinal inflammation and gut microbiome alterations (14, 15). Periods of binge eating when food becomes available may contribute to obesity (16, 17). The psychological worry that accompanies food insecurity may influence other behavioral risk factors for insulin resistance, such as tobacco use (18), inadequate sleep (11), and chronic stress (19), while inadequate food intake can limit energy available to engage in physical activity (12) and may encourage tobacco use as a strategy to cope with hunger pangs. Thus, interventions to support long-term food security for PLWH may substantially reduce risk for insulin resistance through many behavioral pathways other than nutrition.

Moving further upstream, food insecurity can be viewed as a symptom of broader structural forces that indirectly predispose PLWH towards insulin resistance. Unpacking these determinants can enhance the value of social policies, housing programs, and integrated mental health care efforts as necessary investments for enhancing the metabolic health of PLWH. These forces may include community factors (e.g., residential area deprivation and the local food environment), as well as life course events (e.g., early childhood adversity and trauma related to HIV diagnosis), which may each serve as important effect moderators for food insecurity, health risk behaviors, and biologic pathways. For example, adverse childhood experiences (ACEs) (20), such as physical neglect, are important determinants of food insecurity risk in adulthood (21, 22) and disproportionately reported by PLWH (23). ACEs are associated with epigenetic changes (24) as well as many health risk behaviors (25), which can result in biologic consequences, including chronic inflammation (26), insulin resistance (24), and diabetes risk (27, 28) in the general adult population. Therefore, the influence of these upstream risk factors as potential root causes of chronic co-morbidity risk among PLWH are undoubtedly complex, and their impact likely profound (**Figure 1**).

**Figure 1 f1:**
[figure not shown]
Conceptual framework for food insecurity and insulin resistance. Created with BioRender.com.

### Diving downstream: Food insecurity as a potential driver of chronic inflammation among PLWH

At a physiologic, downstream level, additional questions exist for how food insecurity gets “under the skin” to produce pathophysiologic responses associated with insulin resistance. One plausible biological pathway linking upstream forces, food insecurity, and its associated risk behaviors to insulin resistance may be through chronic inflammation. Elevated systemic levels of the inflammatory marker C-reactive protein (CRP) have been linked to food insecurity in the general population (29). Chronic inflammation may be an important contributor to dysglycemia (30), diabetes incidence (31, 32), and other chronic co-morbidities (33) among PLWH, who have higher levels of CRP than the general population (33). Measures of body composition, including body fat and muscle mass, are important biological variable predictors of chronic inflammation (34, 35) and insulin resistance (6, 7, 36, 37). Furthermore, HIV lipodystrophy, body composition changes that are characterized by loss of peripheral fat and deposition of visceral abdominal fat, is also linked to higher fasting insulin levels (38). Central adiposity (independent of BMI) (37) and lipodystrophy (38) in PLWH may directly cause insulin resistance due to accumulation of macrophages in adipose tissue, which secrete proinflammatory mediators (e.g., CRP) that impair glucose uptake into cells (39). Among men with HIV, the residual systematic inflammation that remains after viral suppression may be related to ongoing macrophage activation (40). Among women with HIV, food insecurity has been linked to elevated markers of chronic inflammation, even when controlling for viral suppression and CD4+ T cell count (41).

Additionally, the dietary patterns and periods of prolonged fasting caused by food insecurity may influence the gut microbiome (14), which is increasingly recognized for its role in systemic inflammation and insulin resistance within the general population (42, 43). Thus, food insecurity may exacerbate the consequences of HIV, since infection already disrupts gut homeostasis by reducing CD4+ Th17 and Treg cells in gut-associated lymphoid tissue, which increases intestinal permeability and microbial translocation (44), and drives immune activation and inflammation (45). AIDS history may be particularly detrimental to gut health (44), inflammation (33), and insulin resistance (33). HIV-related alterations in gut microbiome composition, dysbiosis, includes increases in pro-inflammatory *Prevotella* strains, and decreases in anti-inflammatory *Bacteroides* (33). A recent study linked a specific gut microbiome signature with metabolic dysfunction in PLWH, but lacked dietary data (46). Of the few studies that explore the influence of food insecurity or malnutrition on the gut microbiome and its metabolites (14, 47), none have included PLWH.

### Implications for nutrition equity

Malnutrition played a significant role in HIV morbidity and mortality risk in the pre-ART era (48). Community responses to address malnutrition during the early HIV epidemic resulted in the formation of home-delivered meals, other grocery assistance programs, and medical nutrition therapy that typically emphasized intake of high-calorie foods. Over time, many of these programs and services have become institutionalized cornerstones of HIV care across the US. For example, the Ryan White program serves >500,000 unduplicated PLWH nationally (49) and food assistance is an authorized expenditure for Ryan White HIV/AIDS Part A (medical) and Part B (social service) Programs (50).

In contrast with the well-recognized role of food in the prevention and treatment of malnutrition, less is known about how food may be used to reduce chronic co-morbidity risks among PLWH in the modern ART era. Anti-inflammatory dietary patterns may be particularly beneficial for several reasons. Specifically, the Dietary Inflammatory Index (DII^®^), a dietary quality measure that quantifies the inflammatory potential of diet (51), is a useful predictor of chronic inflammation (52), insulin resistance (53–55), and metabolic syndrome (53). Additionally, a high-DII^®^ dietary pattern is associated with food insecurity among lower-income adults in the general population (10). A low-DII dietary pattern is achieved through consumption of wide variety of colorful plant-based foods (fruits, vegetables, nuts, seeds, whole grains, and beans), herbs and spices, and other minimally processed foods. The relationships between food insecurity, inflammatory potential of diet, and insulin resistance among PLWH are yet to be established. An aging cohort of long-term survivors, along with younger generations of more recently diagnosed PLWH, can benefit from HIV-specific nutrition guidance for the prevention of diabetes and related co-morbidities. Research exploring the role of dietary patterns in insulin resistance among PLWH may also be of interest to federal, state, and community stakeholders responsible for management of food assistance programs.

### Objectives

The Nutrition to Optimize, Understand, and Restore Insulin Sensitivity in HIV for Oklahoma (NOURISH-OK) study will result in an integrated, multi-level understanding of how food insecurity contributes to insulin resistance, which is central to the pathogenesis of many chronic co-morbidities in HIV. Its objectives are to: 1) identify the upstream determinants and downstream impacts of food insecurity on pathophysiological processes that may shorten the health span of PLWH, and 2) develop and test a community-driven, science-informed food as medicine intervention to reduce chronic co-morbidity risk among PLWH by addressing key mechanisms in the causal pathway of insulin resistance. We hypothesize that food insecurity will be significantly associated with insulin resistance and that this relationship will be partly mediated by nutritional and non-nutritional health behaviors that increase risk for chronic inflammation. We further hypothesize that these behavioral and inflammatory mediators will significantly differ across all four levels of foods security.

## Methods and Analysis

### Overview of study setting and design

The NOURISH-OK study is being conducted in Oklahoma, a state that ranks among the highest in the nation for adverse childhood experiences (ACEs) (56) and where 54 of its 77 counties are classified as food deserts with all but one county having areas of low food access (57). Among its general adult population, the food insecurity rate (15.6%) exceeds the US rate (11.7%) (58). Its rates of tobacco use, poor diet, and physical inactivity are higher than the national average (59) and the state ranks 2^nd^ highest for obesity, 6^th^ highest for premature mortality (59), and 7^th^ highest for diabetes (59). A recent federal report recognized Oklahoma as being among the top seven states experiencing a high rural HIV burden (60).

The NOURISH-OK study is a 5-year community-based participatory research project that is comprised of three aims. The first aim, initiated in June 2021 with an anticipated enrollment timeline of 18 months, involves a cross-sectional study (n=500) of objective and survey measures to test and refine our conceptual framework of food insecurity and insulin resistance among PLWH. Findings from these analyses will inform the second and third aims of the study, which involve qualitative exploration of significant pathways identified in Aim 1, followed by development and testing of a “food as medicine” intervention to reverse insulin resistance among PLWH that has been prospectively registered (ClinicalTrials.gov Identifier: NCT05208671). Here, we describe the protocol for the first aim of NOURISH-OK.

### Study population and eligibility criteria

The target population for the NOURISH-OK study is PLWH who are eligible for Ryan White-funded programs and reside in Oklahoma. An estimated 3,000 PLWH access one or more Ryan White-funded programs annually (49) and represent the study’s known recruitment pool. Nearly half (47%) of these individuals identify as a racial or ethnic minority, including 23.8% Black, 5.8% American Indian, and 10.1% Hispanic (49). An estimated 79.7% are male with most Ryan White clients aged 25-44 (42.7%) and 45-64 years (49.2%) (49). Study eligibility criteria require participants be HIV-positive residents of Oklahoma, financially eligible for Ryan White services (i.e., household income <400% federal poverty level), prescribed antiretroviral therapy (ART) for at least the past 6 months, and ability to provide a 10-hour fasting blood sample. Study exclusion criteria includes receiving treatment for cancer or end-stage renal disease.

A preliminary food needs study among Oklahoma Ryan White clients in 2012 found a high prevalence of very low (47.6%) and low (19.5%) food security in this population (62). To test our theoretical model of food insecurity as a central mediator linking upstream and downstream determinants of insulin resistance, representation at each level of food security status is needed. Therefore, selection criteria will be based on a food security pre-screening using the 10-item US Adult Food Security Survey Measure (63). Enrollment goals are based on food security status to ensure equal representation across four categories of food security: high (n=125), marginal (n=125), low (n=125), and very low (n=125) (**Figure 2**).

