** *Health-related* **	
Heart rate	Digital automatic blood pressure monitor (Medline)
Oxygen saturation	Pulse oximeter (AccuMed)
Blood pressure	Digital automatic blood pressure monitor (Medline)
HIV history	HIV and AIDS diagnosis dates (chart review); Most recent CD4+ and viral load (chart review)
Co-morbidities	**Physical Health Diagnoses:** Self-reported Hepatitis C, Non-alcoholic fatty liver disease, Pre-diabetes, Diabetes, Renal insufficiency or failure, Stroke, Cardiovascular disease, hypertension (adapted from Behavioral Risk Factor Surveillance Survey 2017) (66). **Mental Health:** Depression (Patient Health Questionnaire-9 (PHQ-9)) (67); Anxiety (Generalized Anxiety Disorder-7 (GAD-7)) (68); Cognitive Function 4-item subscale (MOS-HIV) (69) **Chronic Pain:** 2-item subscale (MOS SF-36) (70)
Medications	HIV antiretroviral therapy (ART); insulin secretagogues; insulin; antibiotics; vitamin or mineral supplements (Combination of chart review and self-reported)
Immunization	COVID-19 vaccination status (self-report)
ART adherence	HIV medication adherence (Self-Rating Scale Item (SRSI) (71)

**Table 2 T2:** NOURISH-OK Study Measures.

Variable	Measure(s) or Method(s)

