** *Downstream Pathology* **	
Chronic inflammation	**High sensitivity C-reactive protein** (MSD - Vplex CRP Kit)
Body composition and malnutrition risk indicators	**Wrist circumference:** Measured in centimeters using Singer tape measure to estimate body frame size (ADAM Medical Encyclopedia) (94) **Grip strength:** Measured using dynamometer (Jamar) as screening indicator for malnutrition (95) **Waist circumference:** Measured in centimeters (Adapted from NHANES 2019-2020 Procedures) (96) **Segmental BIA:** Fat, lean dry mass, and phase angle estimates for truncal, right arm, left arm, right leg, left leg, total body (RJL Systems Quantum V Segmental BIA) (97) **Height and weight:** SECA stadiometer Model #220, SECA Electronic Scale Model #703 **Body mass index:** kg/m^2^
Glucose homeostasis	**Impaired fasting glucose:** Defined as fasting plasma glucose between 100-125 gm/dL (98) **Fasting glucose** (MyBioSource – Glucose ELISA) **Fasting insulin** (MSD - Vplex insulin Kit) **HgbA1c** (A1cNOW^®^ PTS Diagnostics)
Insulin resistance (primary outcome)	**Insulin resistance:** Quantitative Insulin Sensitivity Check Index “QUICKI” = 1/[log(I_0_) + log(G_0_)], where I_0_ is fasting insulin (microunits per milliliter) and G_0_ is fasting glucose (milligrams per decaliter) (99)

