#### Insulin sensitivity

We will use fasting glucose and insulin measures to calculate the quantitative insulin sensitivity check index (QUICKI) as the primary outcome measure for our analyses where a lower value indicates greater insulin resistance (99). Due to its reliability, reproducibility, accuracy, and positive predictive value across a wide range of co-morbidities, the QUICKI is a widely-accepted surrogate index measure of insulin sensitivity that is recommended for larger, community-based research studies when the laborious, clinic-based hyperinsulinemic-euglycemic clamp technique is not feasible (107). The QUICKI uses the empirically-derived equation QUICKI = 1/[log(I_0_) + log(G_0_)], where I_0_ is fasting insulin (μU/ml), and G_0_ is fasting glucose (mg/dl) (99). The QUICKI has been shown to perform equally to or slightly better than the homeostasis model assessment of insulin resistance (HOMA-IR) across the insulin sensitivity-resistance spectrum (108, 109). Additionally, it offers a slight advantage for measuring changes in insulin sensitivity over time (107, 110), which in consideration of our third aim (examining the effects of a food is medicine intervention on insulin resistance), the QUICKI was selected as the most appropriate outcome measure for the NOURISH-OK study.

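### Insulin users remain in the primary QUICKI analysis, although their measured fasting insulin does not show their own insulin-glucose balance

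*Protocol article*

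**What the plan says.** The Insulin sensitivity section uses fasting glucose and insulin "to calculate the quantitative insulin sensitivity check index (QUICKI) as the primary outcome measure for our analyses", with the formula 1/[log(I0) + log(G0)]. Table 2 labels it the primary outcome, and the Final structural equation modeling section makes insulin resistance the endpoint of the model.

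Eligibility rests on HIV status, Oklahoma residence, income, six months of prescribed ART and a 10-hour fasting sample. On exclusions the text reads: "Study exclusion criteria includes receiving treatment for cancer or end-stage renal disease". Diabetes and its treatment are not mentioned there.

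Table 1 shows that such participants are expected. It collects "Self-reported Hepatitis C, Non-alcoholic fatty liver disease, Pre-diabetes, Diabetes" among the co-morbidities, and "HIV antiretroviral therapy (ART); insulin secretagogues; insulin; antibiotics; vitamin or mineral supplements" among the medications. Under Chart review and surveys, participants also confirm the medication lists held in their charts.

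No subsection of Statistical analysis refers to diabetes status or to glucose-lowering treatment. The SEM names AIDS history as effect modifier and invariance group, and the Figure 3 caption refers only to further demographic covariates.

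**The concern.** QUICKI infers sensitivity from the balance between a person's own fasting insulin and glucose. Injected insulin breaks that link. If the assay detects it, measured insulin is too high and the person looks more resistant. If the assay does not, measured insulin is only the remaining endogenous output, and a person with advanced disease can look sensitive. Secretagogues raise insulin output by drug action, so their users are affected too, to a lesser degree. Other glucose-lowering drugs influence QUICKI through treatment, but they do not make the value meaningless.

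The protocol says that food insecurity is associated with diabetes in the general population, and it samples on food security. Affected values may therefore be unevenly spread over the groups being compared. The same outcome is used for the inflammatory-diet analyses within each food security level (125 people each), and the Aim 1 pathways feed Aims 2 and 3.

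**Working it through.** **Inputs from the protocol.** N = 500 as 4 × 125; diabetes in one in ten PLWH (Introduction); SEM sample-size recommendation of up to 460; the QUICKI formula. The logarithm is taken to base 10 (assumption).

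**Plan's own figure.** 4 × 125 = 500, and 500 > 460. The arithmetic is consistent. The plan gives no power calculation and no SD for QUICKI.

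**Size of the affected group.** 0.10 × 500 = 50 with diabetes. The share on insulin is not given. If it is 10-50% of them (assumption), that is 0.10 × 50 = 5 to 0.50 × 50 = 25 people, or 1-5% of the sample. Spread evenly, this is about 1 to 6 per food security group.

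**What happens to the outcome.** QUICKI = 1/(log10 I + log10 G), with illustrative values:

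| Insulin (μU/ml) | Glucose (mg/dl) | Sum of logs | QUICKI |
|---|---|---|---|
| 8 | 90 | 0.903 + 1.954 = 2.857 | 0.350 |
| 4 | 130 | 0.602 + 2.114 = 2.716 | 0.368 |
| 80 | 130 | 1.903 + 2.114 = 4.017 | 0.249 |
| 15 | 110 | 1.176 + 2.041 = 3.217 | 0.311 |
| 30 | 110 | 1.477 + 2.041 = 3.519 | 0.284 |
| 60 | 110 | 1.778 + 2.041 = 3.820 | 0.262 |

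At glucose 130 the value moves by 0.368 − 0.249 = 0.119 according to what the assay sees. The lower insulin reading puts that person above someone at 8 and 90 (0.350). At glucose 110, extra insulin from an injection or a secretagogue lowers QUICKI from 0.311 to 0.284 or 0.262, a fall of about 0.03-0.05 with no change in sensitivity.

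**Possible bias in the very-low versus high contrast.** Bias = (difference in treated share) × (shift in QUICKI). Assume an overall treated share of 5-10%, rising fourfold from high to very low food security, a shift of 0.02-0.04 and an SD of 0.035. None of these is in the protocol.
- Share 5%: 2% against 8%, a difference of 0.06. With shift 0.02 the bias is 0.0012, or 0.03 SD.
- Share 10%: 4% against 16%, a difference of 0.12. With shift 0.04 the bias is 0.0048, or 0.14 SD.
- Insulin users alone, at 5% but with a larger shift of 0.06 (about half of 0.119): 0.06 × 0.06 = 0.0036, or 0.10 SD.
- No gradient: zero.

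The sign follows the sign of the shift, which can go either way. For scale, 125 against 125 detects (1.96 + 0.84) × √(2/125) = 0.35 SD at 80% power.

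**Numbers left after exclusion.** Without insulin users: 500 − 25 = 475 to 500 − 5 = 495, above 460. Without everyone expected to have diabetes: 500 − 50 = 450, below 460.

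**The case against.** The strongest reply is that this is a condensed article. Analysis sets and the handling of concomitant medication usually sit in a full protocol or analysis plan, the SEM diagram is not visible here, and the exclusion list need not be complete. Insulin and secretagogue data are collected, so the means to deal with the problem exist. This lowers the severity, but it does not remove the point. The article itself fixes both the population and the primary outcome rule, and followed as written, that rule gives an uninterpretable value in a subgroup the protocol expects. The article also states such rules for lesser measures: implanted devices and possible pregnancy bar bioimpedance, and smoking and inflammation are named as confounders for carotenoids.

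The protocol also cites QUICKI's accuracy across many co-morbidities. That claim concerns disease states and does not address injected insulin.

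A further objection is that treatment is a consequence of dysglycemia, so excluding or adjusting for treated people conditions on something downstream. This stands. It argues against exclusion of, or adjustment for, all glucose-lowering drugs in the main analysis, and it must be acknowledged as a cost even for insulin users.

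Several stronger readings are tempting but unsupported:
- *Insulin sensitizers go uncaptured.* Table 1 does not name them, but the confirmed chart medication lists are not limited to its classes.
- *Glucose of 126 or more falls into a reference group,* because impaired fasting glucose is "Defined as fasting plasma glucose between 100-125 gm/dL". No section defines such a reference group, and glucose measures are to be analysed as continuous variables.
- *All mediated paths are biased in a known direction.* The stated link to diabetes is for the general population, and no treatment pattern by food security is given.

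**Conclusion.** The point holds for insulin users and, to a lesser degree, for secretagogue users. The stated primary outcome does not fit part of the population that the stated eligibility admits, and no stated analysis deals with it. For other glucose-lowering drugs a reader might infer that QUICKI is invalid as well. It is influenced by treatment, but a drug that really changes sensitivity and is reflected in QUICKI is not a measurement error.

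The distortion is large for an individual (up to 0.119 in the example), but the group is small: 5-25 people if 10-50% of the expected 50 with diabetes use insulin. The effect on the food-security contrast is probably modest, about 0.03-0.14 SD in either direction under the assumed shares, fourfold gradient, shifts and SD, and zero without a gradient. No figure for lost precision is supported, because the protocol gives neither an SD for QUICKI nor a treated share.

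**What to change.** Define the primary QUICKI/SEM analysis set as participants not using insulin. Keep everyone in the descriptive data and in the other outcomes. Pre-specify two sensitivity analyses:
1. all participants;
2. the primary set, further leaving out users of secretagogues and other glucose-lowering drugs, identified from the confirmed medication lists.

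Fix this before QUICKI values are examined, so that the choice is not driven by the data. Recruitment and data collection do not change.

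The cost is a small loss of participants (475-495 remain under the assumption above) and the loss of some of the most severe cases. Conclusions from the primary analysis then apply to people not on insulin, and the report should say so. The second sensitivity analysis could fall to about 450, below the cited 460, which is a further reason not to make it the primary analysis.
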